***VI.2. Statistical analysis***

**Non-normal variables will be log transformed.** They will be adjusted for age, gender and BMI, and residuals will be compared between each group of homozygous individuals at each locus by Student t tests. Since these polymorphisms may influence glycemic traits by affecting BMI, both BMI-adjusted and unadjusted analyses will be reported. Secondary analyses will include exploration of genetic models (dominant, recessive or additive), by including heterozygous individuals and performing ANOVA across the three genotypic groups, with subsequent Bonferroni adjustment for multiple comparisons. The role of self-reported ethnicity will be evaluated with an interaction term; analyses will also be repeated within each self-reported ethnic group, and in the aggregate of groups where minor allele frequencies are comparable. As these experiments involve validation of previous hypotheses, nominal *P* values below 0.05 will be considered statistically significant.

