**Other Partners and Joslin collaborators work with susceptible patient populations.** [name] at the MGH Reproductive Endocrine Unit is currently carrying out a study with about 500 patients with PCOS, only a small fraction of whom (~10%) are on current metformin treatment. Drs. [name] and [name] have an established research program on the metabolic syndrome which comprises approximately 100 subjects with and without HIV infection. [name] has been following a cohort of ~200 women with a history of gestational diabetes mellitus (GDM) ([80](#_ENREF_80)). Finally, we have access to 1,004 non-diabetic subjects formerly enrolled in a Partners-Roche Consortium who have consented to diabetes-related genetic investigation, 25% of whom have BMI >30 kg/m^2^. These cohorts can be further expanded, if necessary, with additional help from the MGH and Brigham Obesity Clinics. At the Joslin Diabetes Center, family members of the diabetic patients will also be recruited.

As the study aims to test the effect of specific genetic variants on pharmacological response, recruitment efforts will also include queries within an institutional biorepository containing samples adequate for genotyping and demographic information on individuals interested in participating in clinical trials. Individuals who have already indicated interest in participating in future studies and given consent for genotype-directed call back into future research studies will be contacted first by mail to assess their interest in participating in SUGARMGH and then, unless otherwise indicated, by phone.

In the event that an individual does not qualify to participate in the study, we will ask if they would like to be contacted by collaborators involved in other research studies.

In the event that recruitment lags, we will advertise outside of the Partners and Joslin networks. This may include posting flyers, internet advertising, newspaper ads and any other forms of displaying the approved flyer.

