***V.7. Subject confidentiality***

**At all moments, the privacy of research subjects will be protected.** Subjects will receive a coded, anonymous numerical identifier that will link their anthropomorphic, biochemical and genetic measurements to each other but not to the individual. The key will be stored in the PI’s office in a locked cabinet and in his password-protected hard drive. A code will also be used to mark his/her self-reported ethnic group. If the OGTT suggests the presence of diabetes in a previously undiagnosed subject, the subject (and his/her primary care physician if agreed beforehand) will be contacted for appropriate follow-up and confirmation.

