***VI.3. Power calculations***

**Our power calculations suggest that we will need to enroll ~750 subjects.** Based on our own multi-ethnic data, we have estimated a minor allele frequency of 0.32 for the risk T allele at rs7903146 *TCF7L2* and 0.35 for the risk K allele at *KCNJ11* E23K. Assuming Hardy-Weinberg equilibrium, the proportion of subjects carrying the risk homozygous genotype at either locus will be ~10% and ~12% respectively. With the difference in insulinogenic index between CC and TT homozygotes at rs7903146 *TCF7L2* documented by Saxena *et al.,* (see Section C.3 above), 750 subjects should provide >80% power to detect the same difference at a one-sided alpha of 0.05. Similarly, assuming that the difference in insulin sensitivity after one year of metformin treatment by E23K genotype is also detectable in the acute setting, 750 subjects provide >90% power at the same one-sided alpha of 0.05 (73% for a two-sided test). With regard to the sulfonylurea challenge, this sample size has >99% power to detect a 10% difference in trough glucose between genotypic groups at a one-sided alpha of 0.05, and 94% power to detect a 20% difference in peak insulin at a one-sided alpha of 0.05.

While these power calculations apply to a study population of a single ethnic group, expanding our study to include a multi-ethnic population would require enrollment of ~1,000 subjects.

1. **Risks and DIscomforts**

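### The main genotype comparison in a multi-ethnic sample is not adjusted for ethnicity, and the ethnicity analyses listed beside it are not said to govern

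*Protocol*

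**What the plan says.** Section VI.2 sets out the main analysis as follows: "They will be adjusted for age, gender and BMI, and residuals will be compared between each group of homozygous individuals". The comparison uses Student's t test and is made separately for each locus. The covariate list stops at age, gender and BMI.

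Ethnicity comes later in the same paragraph: "The role of self-reported ethnicity will be evaluated with an interaction term; analyses will also be repeated within each self-reported ethnic group". A further repeat, restricted to some of the groups, is to be run "in the aggregate of groups where minor allele frequencies are comparable". The word also marks these as additions to the main comparison. VI.2 does not define comparable and does not say which result decides if the pooled and within-group answers differ. The threshold is a nominal one: P "values below 0.05 will be considered statistically significant".

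The sample is expected to be multi-ethnic. Section VI.3 ties 750 subjects to a single ethnic group and states that "expanding our study to include a multi-ethnic population would require enrollment of ~1,000 subjects"; section VII.1 then gives 1,000 as the number to enrol. The allele frequencies in VI.3 (0.32 for *TCF7L2*, 0.35 for *KCNJ11*) are single pooled values from multi-ethnic data. Section V.7 confirms that the variable will exist: "A code will also be used to mark his/her self-reported ethnic group".

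**The concern.** A third variable confounds a comparison of unrelated people by genotype if it is associated with both the genotype and the trait. Ethnic group can do this: where allele frequencies differ, the two homozygous groups have different ethnic mixes, and any trait difference between the ethnic groups then appears as a genotype effect. Section I.3.a recognises this hazard, crediting the family-based parts of the group's earlier samples with robustness to population stratification. The t test in VI.2 has no such protection.

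An interaction term does not supply it. That term asks whether the genotype effect differs between ethnic groups; it leaves the residual comparison in the whole sample as it was.

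Both the effect estimate and the type I error of the primary comparison are at stake. The bias does not shrink as the sample grows, so a larger N makes a spurious difference easier to declare significant.

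**Working it through.** **1. The plan's own figures.** Hardy-Weinberg shares are 0.32² = 10.2% and 0.35² = 12.25%, matching the stated ~10% and ~12%. For the insulinogenic index, section I.3.c gives 0.61 ± 0.71 (TT) against 1.00 ± 1.84 (CC), a difference of 0.39. At N = 750 there are 76.8 TT and 346.8 CC. With unequal variances, SE = √(0.71²/76.8 + 1.84²/346.8) = 0.128, and one-sided power is Φ(0.39/0.128 − 1.645) = 92%. The stated >80% is therefore met. With a pooled SD of 1.69 it would be 57%. The point below does not depend on this figure.

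**2. Inputs for the bias.** From the documents: N = 1,000 and pooled allele frequency of about 0.32. As a proxy: 77.7% in one group and 22.3% in the rest, from Table 1 in III.1, which describes only diet-treated patients with diabetes. Assumed, because the documents do not give them: the allele frequency in each group (q₁ majority, q₂ minority) and the trait gap D between groups, in SD units, left after adjustment for age, gender and BMI. There is no true genotype effect.

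**3. Formulas.**
- TT count = N(0.777 q₁² + 0.223 q₂²); CC count = N(0.777(1−q₁)² + 0.223(1−q₂)²)
- Bias = D × (minority share among CC − minority share among TT)
- SE = √(1/TT + 1/CC); shift s = bias/SE
- Two-sided type I error = Φ(s − 1.96) + Φ(−s − 1.96)

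**4. One case in full** (q₁ = 0.355, q₂ = 0.20, pooled 0.320). TT = 106.8, CC = 466.0. Minority share is 8.92/106.8 = 8.3% of TT and 142.7/466.0 = 30.6% of CC, a difference of 0.223. SE = 0.107. At D = 0.5 the bias is 0.111 SD and s = 1.04, so the error is 18.0%.

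**5. Range at N = 1,000, nominal 5%.**

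| q₁ / q₂ | D (SD) | Bias (SD) | Two-sided error |
|---|---|---|---|
| 0.32 / 0.32 | any | 0 | 5.0% |
| 0.34 / 0.25 | 0.1 | 0.014 | 5.2% |
| 0.34 / 0.25 | 0.3 | 0.041 | 6.6% |
| 0.355 / 0.20 | 0.1 | 0.022 | 5.5% |
| 0.355 / 0.20 | 0.3 | 0.067 | 9.6% |
| 0.355 / 0.20 | 0.5 | 0.111 | 18.0% |
| 0.38 / 0.10 | 0.5 | 0.179 | 40.4% |

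A simulation (4,000 runs per scenario, N = 1,000, Student t test on homozygotes) agrees with the approximation: for example 12.1% for a frequency gap of 0.20 with D = 0.3, where the formula also gives 12.1%. With an ethnicity main effect added, the simulated error was 4.3% to 5.3% in every scenario.

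**6. How well the within-group repeats can stand in.** This uses the Table 1 proxy, the pooled frequency 0.32 and the I.3.c values.
- Majority, about 777 subjects: 79.6 TT, 359.3 CC, SE 0.126; one-sided power 93% (58% with the pooled SD).
- Remainder, about 223 subjects: 22.8 TT, 103.1 CC, SE 0.234; power 51% one-sided and 38% two-sided (26% and 17% with the pooled SD). At a group frequency of 0.20 there would be only about 9 TT (223 × 0.04).

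**The case against.** The strongest reply is that VI.2 already contains the protection. Repeating the analysis within each self-reported group removes confounding between those groups. Pooling only groups with comparable allele frequencies removes one of the two conditions for the bias, as the first row of the table shows. That grouping criterion is allele frequency rather than outcome, so leaving comparable undefined does not by itself inflate the error rate. In the majority group the repeat is also close to full size: about 777 subjects, against the 750 that VI.3 requires for a single ethnic group.

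Most of this stands. A reader might infer that the plan ignores ethnicity, or that no adequately sized ethnically homogeneous analysis exists. The text supports neither. What remains is that these analyses are additions. The test that VI.2 puts first is unadjusted, and no rule says the others override it.

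A reader might also infer a second path to bias from biorepository participants who have "given consent for genotype-directed call back into future research studies". Section III.1 gives no numbers for this source and does not say that homozygotes will be oversampled. Selecting on genotype does not in itself bias a comparison by genotype. That inference is not supported and forms no part of this point.

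**Conclusion.** The point holds as a defect in how the primary comparison is specified. The main t test omits a recognised confounder in a sample planned to be multi-ethnic, and the analyses that would guard against it are not given precedence.

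The size is unknown. Bias needs both an allele-frequency gap and a trait gap that survives adjustment for age, gender and BMI, and the protocol states neither. A reader might take 18% or 40% as the error rate of this study. The documents do not support that: those figures use an assumed trait gap of 0.5 SD, the largest considered, and 40% also assumes the widest frequency gap in the table. With small gaps the error stays near 5%. Nor should error rates computed at N = 750 be applied to the multi-ethnic plan, since VI.3 links that number to a single ethnic group.

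The case for changing the text rests on a plausible bias of uncertain size in the primary comparison and a remedy that costs almost nothing.

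**What to change.** In VI.2, add self-reported ethnicity as a main effect to the primary adjustment, alongside age, gender and BMI. Alternatively, name the ethnicity-stratified combined estimate as the primary result. Under either choice, state that this result governs, and keep the interaction term and the within-group analyses as secondary.

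The cost is one sentence and a few degrees of freedom. Section V.7 already provides for coding self-reported ethnic group, so no new data are needed.

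### VI.2 tests genotype on residuals from a model that omits genotype, which shrinks covariate-adjusted effects by the R² of genotype on age, gender and BMI; the effect is minor, and one joint regression removes it

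*Protocol*

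**What the plan says.** Protocol VI.2 log-transforms non-normal endpoints and then sets the primary comparison: "They will be adjusted for age, gender and BMI, and residuals will be compared between each group of homozygous individuals". The test named for this comparison is Student's t, applied locus by locus. As worded, the adjustment comes first and leaves genotype out; genotype enters only when the residuals are compared. The section does not say whether the adjustment is fitted in all subjects or only in homozygotes.

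Two further statements in VI.2 bear on this. On BMI: "Since these polymorphisms may influence glycemic traits by affecting BMI, both BMI-adjusted and unadjusted analyses will be reported". On ethnicity: "The role of self-reported ethnicity will be evaluated with an interaction term", with analyses also repeated within each self-reported ethnic group. The section gives no estimate of how strongly genotype is associated with age, gender or BMI, and no rule for reading a gap between the BMI-adjusted and unadjusted results.

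**The concern.** When an outcome is residualised on covariates and the exposure is not, the first step credits to the covariates any part of the exposure effect that is correlated with them. The second step cannot recover it. A single regression containing genotype and the covariates does not have this problem.

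Two things are at stake. The first is a downward bias in each covariate-adjusted genotype difference, by an amount that depends on the genotype-covariate association. The second is the side-by-side BMI comparison. VI.2 reports both versions because the variants may act through BMI. If genotype is associated with BMI, the two-step method makes the adjusted effect smaller than the unadjusted one even if BMI does nothing to the trait. The artefact grows with the very link that the comparison is meant to look at.

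**Working it through.** **Inputs.** VI.3 says "we will need to enroll ~750 subjects", "estimated a minor allele frequency of 0.32 for the risk T allele" at TCF7L2 and "0.35 for the risk K allele" at KCNJ11. Table 1 (III.1) gives a BMI SD of 7.6 kg/m² in diet-treated patients, used here only to convert SD units. The BMI gap D between homozygote groups, in SD units, is not in the protocol; the values below are assumptions.

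**Plan's own figures.** 0.32² = 10.24% and 0.35² = 12.25%, which reproduce the roughly 10% and 12% risk-homozygote shares in VI.3. Of 750 subjects, TCF7L2 gives 76.8 TT and 346.8 CC (0.68² = 46.24%). KCNJ11 gives 91.9 KK and 316.9 EE (0.65² = 42.25%). The risk group's share p of the homozygotes is 76.8/423.6 = 0.181 and 91.9/408.8 = 0.225. This point disputes no figure stated in the plan.

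**Algebra.** Let M be the residual-maker for the covariates and intercept, and G the homozygote indicator.

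- Joint model: β = G′My / G′MG.
- Two-step: difference = G′My / Σ(G − mean G)².
- Ratio, two-step to joint: G′MG / Σ(G − mean G)² = 1 − R².

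This is exact when step 1 is fitted in the homozygotes. Fitting it in all subjects gives a similar but somewhat smaller shrinkage for an additive effect.

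**Size of R².** For one covariate with gap D, R² = k/(1 + k), with k = p(1 − p)D². Here p(1 − p) is 0.148 for TCF7L2 and 0.174 for KCNJ11. Three covariates add about 3/(n − 1) by chance: 3/422.6 = 0.7% for the TCF7L2 homozygotes.

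| D (SD) | BMI gap (kg/m²) | R², TCF7L2 | R², KCNJ11 | TCF7L2 with chance |
|---|---|---|---|---|
| 0 | 0 | 0 | 0 | 0.7% |
| 0.2 | 1.5 | 0.6% | 0.7% | 1.3% |
| 0.4 | 3.0 | 2.3% | 2.7% | 3.0% |
| 0.8 | 6.1 | 8.7% | 10.0% | 9.4% |

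**Simulation check.** Settings: 750 subjects, allele frequency 0.32, homozygotes compared, true homozygote difference 0.38 residual SD, 1,000 runs per setting (3,000 under the null).

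| D (SD) | Two-step/joint, step 1 in homozygotes | Two-step/joint, step 1 in all subjects |
|---|---|---|
| 0 | 0.993 | 0.996 |
| 0.2 | 0.987 | 0.990 |
| 0.4 | 0.970 | 0.979 |
| 0.8 | 0.905 | 0.931 |

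- Power loss against the joint model: at most about 1 point up to 0.4 SD, and about 1 to 3 points at 0.8 SD (for example 83.0% against 80.0%).
- Type I error of the two-step test: 5.5%, 4.6% and 4.1% at gaps of 0, 0.2 and 0.8 SD. The simulation standard error is √(0.05 × 0.95/3000) = 0.4 points, so there is no inflation; at 0.8 SD the test is slightly conservative.

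**BMI comparison when BMI has no effect on the trait** (step 1 in homozygotes; the unadjusted figure comes from a regression on genotype, age and gender):

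| D (SD) | Without BMI | Joint with BMI | Two-step with BMI | Apparent drop, two-step |
|---|---|---|---|---|
| 0.2 | 0.378 | 0.379 | 0.374 | 1% |
| 0.4 | 0.375 | 0.375 | 0.364 | 3% |
| 0.8 | 0.386 | 0.387 | 0.350 | 9% |

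When BMI was given a real effect (0.4 SD of trait per SD of BMI) at a 0.4 SD gap, the estimate fell from 0.537 without BMI to 0.375 jointly and 0.364 two-step. The artefact is then 0.011 of a drop of 0.173; the rest is genuine.

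**Small ethnic groups.** The protocol gives no subgroup sizes. Assume 74 subjects, of whom about 40 are homozygous at KCNJ11 frequencies (74 × 0.545). Chance alone then gives 3/73 = 4% with step 1 in all of them, or 3/39 = 8% with step 1 in the homozygotes.

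**The case against.** The strongest reply is that the bias is real in algebra and small in practice. No genotype-covariate association is documented. VI.2 says only that the variants may affect BMI, and suggests no link with age or gender. Recruitment sources with different age and BMI create such a link only if genotype frequency also differs between sources, which the protocol does not show. At modest gaps the shrinkage is a small fraction of the sampling error. With 1,000 subjects and allele frequency 0.35 (122.5 against 422.5 homozygotes), the standard error of a difference is √(1/122.5 + 1/422.5) = 0.10 SD. A 1.3% shrinkage of an assumed 0.30 SD effect is 0.004 SD, about 4% of that. In the assumed subgroup of 74 (about 9 against 31 homozygotes) the standard error is about 0.38 SD, and 8% of 0.30 is 0.024 SD, about 6% of it. All of this stands and sets the severity.

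A reader might infer more in four places, and the protocol does not support it:

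- **That a false mediation finding is planned.** VI.2 plans no mediation analysis; it only says that both results will be reported.
- **That the ethnicity interaction cannot be fitted.** The t test cannot hold it, but a two-way model on the residuals could, and VI.2 does not place the interaction inside the t test.
- **That false positives increase.** They do not, and shrinkage by (1 − R²) cannot reverse a sign.
- **That the SDs in I.3.c (0.71 against 1.84) rule out equal variances.** They are raw-scale and for one endpoint, and VI.2 log-transforms non-normal variables first. If the values were lognormal around the stated means (0.61 and 1.00), the log-scale SDs would be √ln(1 + (0.71/0.61)²) = 0.93 and √ln(1 + 1.84²) = 1.22: unequal, but closer.

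What the reply does not do is give the two-step method any advantage over one joint regression.

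**Conclusion.** The point holds as a minor weakness in a method that the protocol states. The two-step estimate is the jointly adjusted difference times (1 − R²). For TCF7L2 in the full sample the shrinkage is under 1% without any genotype-covariate association, about 1 to 3% at a BMI gap of 0.2 to 0.4 SD, and about 9% only at 0.8 SD, roughly 6 kg/m² between homozygote groups. The KCNJ11 figures are slightly higher.

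These sizes rest on assumed BMI gaps, Hardy-Weinberg shares and, for the simulation, an additive effect. A real association of genotype with age or gender would add to R². It would go too far to say that every primary effect is materially attenuated: that needs an association of a size the protocol does not document, and results not adjusted for any covariate are not affected at all. The case for changing the text is that the bias is avoidable at almost no cost, and that it grows with the genotype-BMI link that VI.2 itself raises.

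**What to change.** In VI.2, replace the residual step with one linear model per endpoint and locus: (log) endpoint = homozygote group + age + gender + BMI. Report the genotype coefficient with its confidence interval, and refit without BMI for the result not adjusted for BMI. The planned ethnicity interaction can go in the same model. Heteroscedasticity-robust standard errors are a sensible precaution, given the unequal raw-scale SDs of the insulinogenic index, although the log transformation may narrow that gap.

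The cost is one sentence of protocol text and a few degrees of freedom. No subjects, visits or data are added.

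### VI.2 repeats each genotype comparison in every ethnic group and in an aggregate of groups, yet does not restrict the nominal P<0.05 rule to one deciding population

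*Protocol*

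**What the plan says.** Protocol VI.2 sets the main test: after adjustment for age, gender and BMI, "residuals will be compared between each group of homozygous individuals at each locus by Student t tests". Secondary analyses bring in heterozygotes by "performing ANOVA across the three genotypic groups, with subsequent Bonferroni adjustment for multiple comparisons".

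On ethnicity, VI.2 says "The role of self-reported ethnicity will be evaluated with an interaction term", and in the same sentence that "analyses will also be repeated within each self-reported ethnic group, and in the aggregate of groups where minor allele frequencies are comparable". It closes by stating that "nominal *P* values below 0.05 will be considered statistically significant", on the ground that the experiments validate earlier hypotheses.

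VI.3 gives power at a one-sided 0.05, for example "750 subjects should provide >80% power to detect the same difference at a one-sided alpha of 0.05". It then limits these figures to one ethnic group and says that "expanding our study to include a multi-ethnic population would require enrollment of ~1,000 subjects".

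**The concern.** For one locus and one endpoint, VI.2 yields a test in all subjects, one test per ethnic group and one in an aggregate of groups. The significance rule follows directly and names no population. The interaction term is planned but is not made a condition for reading the within-group tests.

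The rationale for a nominal threshold does not reach the ethnic groups. The hypotheses and Specific Aims (section headed Statement of Hypothesis and Specific Aims) concern loci, drugs and phenotypes; none is specific to an ethnic group. The metformin-by-E23K observation to be followed up came from a multi-ethnic cohort (I.3.b and I.3.c).

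At stake is a locus that is null overall but is reported as a significant drug-gene effect in one ethnic group. Section I.3.c says that the study is meant to prepare an outcomes-based trial, so such a finding could misdirect it. The tests can also disagree, and VI.2 does not say which one answers the aim.

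**Working it through.** **Inputs from the protocol.** Threshold 0.05 (VI.2). Populations: all subjects, each ethnic group, one aggregate (VI.2). Enrolment about 1,000 if multi-ethnic, and risk-allele frequency 0.32 for *TCF7L2* (VI.3). Caucasian share 77.7% in the diet-treated source cohort (Table 1).

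**Assumptions.** The protocol gives neither the number nor the sizes of the ethnic groups. I take K = 2, 3 or 4, with 77.7% in the largest group, and equal sizes as a check. A positive locus means P<0.05 in any population.

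**Step 1, the stated rate.** One all-subject test under the null gives 0.050.

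**Step 2, within-group tests alone.** These are independent, so the chance of at least one positive is 1 − 0.95^K:
- K = 2: 1 − 0.9025 = 0.098
- K = 3: 1 − 0.8574 = 0.143
- K = 4: 1 − 0.8145 = 0.186

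**Step 3, all tests together.** The all-subject statistic is Σ√(wᵢ)·zᵢ, with wᵢ the group shares and zᵢ independent standard normal. The aggregate is built the same way from a subset of groups. One million null replicates, two-sided, give:

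| K | All-subject + groups | Adding an aggregate | Ratio to 0.05 | Equal group sizes |
| --- | --- | --- | --- | --- |
| 2 | 0.112 | same (no new subset) | 2.2 | not run |
| 3 | 0.156 | 0.162 | 3.2 | 0.172 |
| 4 | 0.199 | 0.204 | 4.1 | 0.216 |

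One-sided testing gives nearly the same: 0.109, 0.157 to 0.163 and 0.199 to 0.206.

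**Step 4, the aggregate.** In the table it adds about 0.005. With the all-subject test and an aggregate but no within-group tests, the chance is 0.063 to 0.093 over the layouts tried (3 to 5 groups). The within-group tests drive the result.

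**Step 5, what a small group can show.** With four groups and the remainder split equally, a minor group has 1,000 × 0.223/3 ≈ 74 subjects and 74 × 0.32² ≈ 8 risk homozygotes. An effect with 80% one-sided power at 750 has expected z = 1.645 + 0.842 = 2.487. At 74 subjects this is 2.487 × √(74/750) = 0.78, giving power of about 19% one-sided (12% two-sided). Such a group adds a full 5% chance of a false positive and little chance of a true one.

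**Step 6, is the all-subject test as written a safe deciding test?** It adjusts for age, gender and BMI but not ethnicity. Assume 1,000 subjects in two groups (777 and 223), risk-allele frequencies 0.32 and 0.15, and a trait difference of 0.4 SD unrelated to the locus.
- Risk homozygotes: 79.6 + 5.0 = 84.6, of whom 5.9% are from the smaller group.
- Other homozygotes: 359.3 + 161.1 = 520.4, of whom 31.0% are from the smaller group.
- Spurious difference: 0.4 × (0.310 − 0.059) = 0.100 SD; standard error about 0.119; expected z = 0.84.
- Two-sided null rejection rate: about 0.13.

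With frequency 0.05 in the smaller group the shares are 0.7% and 35.9%. The spurious difference is 0.141, the standard error 0.121, z = 1.16, and the rejection rate about 0.21. The allele frequencies for the smaller group and the 0.4 SD are assumptions.

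**The case against.** The strongest reply is that the repeats are consistency checks. VI.2 says the analyses will *also* be repeated, which makes the all-subject analysis the base, and the repeats share a sentence with the interaction term. Nothing says that a positive result in any one population makes a locus positive. Subgroup status is often left to a statistical analysis plan, and the protocol calls the work a pilot. Much of this stands, and it makes the inflation conditional. It does not remove the point, because VI.2 itself states a significance rule and does not restrict it.

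A second reply is that the repeats protect against population stratification, a problem that I.3.a recognises, and that relying only on the all-subject test as written could be worse. This is right, as step 6 shows, and it shapes the fix.

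Three stronger readings are tempting and are not supported:
- A reader might infer that error is inflated two- to fourfold as a fact of the plan. It is not: the factor needs the any-population rule and assumed groups.
- A reader might infer from VI.3 that a within-group analysis is primary, since its power figures are for a single ethnic group and 77.7% of 1,000 lies near 750. VI.3 does not reserve 750 subjects for one group, and recruitment reaches well beyond the cohort in Table 1 (III.1, III.2), so the closeness is coincidence.
- A reader might infer that the aggregate is picked to favour a result. It is chosen by allele frequency, not outcome, and adds little.

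**Conclusion.** The point holds in conditional form. VI.2 joins repeated analysis populations to an unrestricted nominal threshold. The stated rationale does not cover claims in a single ethnic group, and the ANOVA Bonferroni step does not cover populations. If significance in any population may be claimed, one null locus and endpoint is declared positive with probability about 0.11, 0.16 or 0.20 for two, three or four groups, against 0.05. These figures rest on the assumed number and sizes of groups and on a normal approximation. They count a single locus, endpoint and form of analysis.

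Naming the all-subject test exactly as written would not be enough, because it omits ethnicity. The deciding test needs ethnicity in it.

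**What to change.** In VI.2, name one deciding test for each locus and endpoint: the homozygote comparison in all subjects, adjusted for or stratified by self-reported ethnicity in addition to age, gender and BMI. Limit the nominal P<0.05 sentence to that test.

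Describe the within-group and similar-allele-frequency analyses as supportive consistency checks, reported as estimates with confidence intervals and with no stand-alone claim of significance. Interpret differences between groups through the genotype-by-ethnicity interaction term already planned.

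The cost is wording, with no extra subjects or data. A result in one ethnic group can no longer be called significant by itself, and ethnicity adjustment uses a few degrees of freedom.
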